### **Screening visit 1**

Male and female healthy volunteers who accomplish the inclusion criteria and none of the exclusion criteria are eligible for the study and will undergo the following investigation procedures in the screening visit, after signing the informed consent:

- Detailed explanation of the study procedures, including the intake of alcohol under medical supervision
- Check inclusion and exclusion criteria
- Check for demographic data, medical and surgical history and concomitant medication
- Date of birth, gender, smoking status, alcohol consumption
- Body weight and body height
- Vital signs: resting pulse and blood pressure
- Physical examination
- Pregnancy test in women of childbearing age.
- Blood sampling
- Distribution of the material for the gut permeability urine test and stool

sampling

## **Visit 2**

Subjects will be informed about the nature of the study, including the intake of alcohol. The patients have to sign that they will not use a car or a machine on the day of the study. They have to state how they will travel home after the study (either taxi, public transport or being picked up by an adult friend or family member).

As part of this visit the following procedures will be performed:

- Body weight
- Vital signs: resting pulse and blood pressure
- Physical examination
- Pregnancy test in women of childbearing age
- Alcohol breath test
- Blood sampling via a venous access line before alcohol consumption and every hour for 4 hours.
- Consumption of 2 ml vodka 40% v/v ethanol/kg body weight in a total volume of 300 ml orange or strawberry juice (alcohol group) or consumption of 2 ml tap water/kg body weight in a total volume of 300 ml orange or strawberry juice (control group), or 75g of fructose in 300ml of water, or a mixed caloric drink (Fortimel compact, 10kcal/kg)

Subjects from the alcohol group will be monitored at the Clinical Research Center until the alcohol breath test is below 0.5 ‰. Subjects will be provided with a taxi voucher.

## **Visit 3**

24h after visit 1 they patients will have to perform the gut permeability urine test for 5h at home, collect a stool sample and fill in the self-administered hangover questionnaire and will have to bring the urine sample, the stool sample and the questionnaire to the trial site.

## 8 Methods

### 8.1 Sample size

In order to determine the magnitude of effect on gut permeability and innate immune function by a single alcohol binge, we intend to perform a pilot study on 46 healthy volunteers (16 in the alcohol group, 30 in the control groups).

### 8.2 Tests

The assays described in this section are the current state of the art. It is possible that the methodology changes until analysis or that assays need to be exchanged for technical reasons.

#### 8.2.1 Gut permeability and inflammation

A ready-to-use solid-phase sandwich ELISA (Immundiagnostik AG, Bensheim, Germany) is used to detect DAO, Zonulin and Calprotectin in serum and stool samples. The test is performed according to the manufacturer's instructions.

Lactulose/Mannitol test: After overnight fasting, the patient drinks a solution of 100 ml water containing 10g lactulose, 1g D-mannitol and 20g sucrose. Urine is collected over 5 hours while fasting is continued for 3 hours after study start. The urine volume collected during the 5 hours is wrote down and 1ml aliquots are frozen immediately at -80°C with 10% of a 1% thimerosal solution for subsequent analysis by NMR spectroscopy.

#### 8.2.2 Bacterial products

##### Endotoxin, peptidoglycan, bacterial DNA

Bacterial products (endotoxin, peptidoglycan and bacterial DNA) are detected in serum using HEK-Blue hTLR4, HEK-Blue hNOD2 and HEK-Blue hTLR9 reporter cells (Invivogen, Toulouse, France), respectively. Cells are cultured according to manufacturer's instructions. For detection, 5x10^4 cells/well are transferred to 24-well plate (Nalgene/Nunc, Rochester, USA) and incubated with 2ml selection medium for 24 hours. Selection medium is replaced by 950µl HEK-Blue Detection (Invivogen, Toulouse, France) and 50µl standards, blanks, spikes and samples. After 21 hours photometrical assessment of the supernatant at 650nm is used for analysis. For

quantification a standard 1:2 serial dilution of either Endosafe Endotoxin standards (Charles River, Wilmington, USA) ranging from 50EU/ml to 3.13EU/ml, L18-MDP (Invivogen, Toulouse, France) ranging from 10ng/ml to 0.625ng/ml for peptidoglycans, or ODN2006 (Invivogen, Toulouse, France) ranging from 50µM to 3.13 µM for bacterial CpG motifs is used. An increasing concentration of recombinant alkaline phosphatase is added (0, 250 and 500 U/L) to each sample and linear regression is used to account for endogenous alkaline phosphatase in serum.

Endotoxin binding proteins

A ready-to-use solid-phase sandwich ELISA (Hycult biotechnology, Uden, Netherlands) is used to detect LBP and sCD14 levels in EDTA plasma samples.

**8.2.3 Neutrophil function**

The Phagoburst® kit (Glycotope, Heidelberg, Germany) will be used to determine activation and burst profiles of neutrophils and monocytes by flow cytometric analysis. Cells will be discriminated forward-side-scatter characteristics. Phagocytosis will be assessed by Phagotest® (Glycotope, Heidelberg, Germany), a flow cytometric analysis using FITC-labelled *E. coli* bacteria.

**8.2.4 Statistical analysis**

Data will be analyzed with SPSS 21. Data will be described using median and quartiles or percentage of the total group as appropriate. All data will be checked for normal distribution. Differences in dependent categorical variables (questionnaire data) will be assessed by McNemar test. Differences in continuous variables over time (all other variables) will be assessed by ANOVA or Friedman tests, depending on the distribution of the data. Bonferroni correction for multiple testing will be used. Pearson or Spearman correlation, depending on the distribution of data, will be used to assess correlation between variables (blood alcohol, gut permeability, bacterial translocation, neutrophil function, oxidative stress). All tests will be performed on a 5% significance level.

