## 6.2 Exclusion criteria

- Alcohol abuse
  - Alcohol Use Disorders Identification Test  $\geq 8$  in men or  $\geq 7$  in women
  - or
  - CAGE test  $\geq 2$  (both men and women)
- Elevated liver function test
- Any disease or medication that does not allow concomitant consumption of alcohol
- Women: pregnancy and lactation

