## 7 Visit Schedule

Volunteers will undergo 1 screening visit and 2 study visits.

The screening visit duration is approximately 1 hour, the first study visits will last at least 5 hours with an optional observation/recovery period thereafter until the alcohol breath test is below 0.5 ‰. On the next day patients will have to perform the gut permeability test at home and will deliver the urine sample together with a stool sample and a questionnaire to the trial centre.

### Table 1

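### Section 8.2.4 assigns McNemar's paired test to the questionnaire data, but as scheduled each person completes the questionnaire once, in unmatched groups, so there are no pairs to test (minor)

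*Protocol*

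**What the plan says.** Protocol Section 8.2.4 gives one rule for categorical data: "Differences in dependent categorical variables (questionnaire data) will be assessed by McNemar test". The next rule sends the continuous variables, measured over time, to ANOVA or Friedman tests. McNemar is thus the only test the protocol offers for the questionnaire.

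On collection, the Visit 3 text in Section 7 has subjects do the urine permeability test at home and "collect a stool sample and fill in the self-administered hangover questionnaire". The opening paragraph of Section 7 agrees: on the day after the first study visit, subjects "will deliver the urine sample together with a stool sample and a questionnaire to the trial centre". Both places describe a single questionnaire.

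On design, Section 7 says "Volunteers will undergo 1 screening visit and 2 study visits". Visit 2 is the only visit at which a drink is given. Section 8.1 gives the group sizes as "16 in the alcohol group, 30 in the control groups".

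**The concern.** A paired test presupposes that the same item is answered twice by one person, or that each person has a matched partner. Section 8.2.4 calls the questionnaire variables dependent, but the schedule collects them once and the groups are independent. The analysis section and the visit schedule do not fit together.

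What is at stake is limited but real. An analyst who follows the protocol literally has no data layout on which to run the stated test, and no other test is given for this instrument. The analysis would be dropped, or chosen once the answers are known. The comparison the data could support, alcohol against control on the day after the drink, is not stated for the questionnaire.

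**Working it through.** No figure in the protocol needs reproducing here. The check is whether the data required by the test exist.

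**What the test needs.** McNemar's statistic is (b − c)² / (b + c). Here b and c count the pairs whose two binary answers differ in one direction and in the other. Without pairs, b and c are undefined.

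**Hangover questionnaire administrations per person.**

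| Place in the protocol | Questionnaire listed? | Count |
|---|---|---|
| Section 7, Screening visit 1, procedure list | No | 0 |
| Section 7, Visit 2, procedure list | No | 0 |
| Section 7, Visit 3 | Yes | 1 |
| Table 1, schedule of assessments | No row for it | none |

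The total is 0 + 0 + 1 = 1 per person. One administration gives no before/after pair, so there are 0 such pairs among 16 + 30 = 46 subjects. Visit 3 is taken here as the day after the drink, as the opening of Section 7 describes. The Visit 3 text and Table 1 label the reference visit differently, but that does not change the count.

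**Could another instrument supply the pair?** The "Alcohol Use Disorders Identification Test" and the CAGE test appear in Section 6.2 as exclusion criteria. They are different instruments from the hangover questionnaire, and no repeat is planned, so they neither pair with it nor form pairs of their own.

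**Could subjects be paired across groups?** Section 8.1 gives 16 alcohol and 30 control subjects. The Visit 2 text lists the control drinks (tap water in juice, fructose in water, a mixed caloric drink) as alternatives to the alcohol drink. No crossover and no matching is described, and the group sizes differ. Between-group pairs: 0.

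**Could *dependent* mean outcome variable?** Then the comparison would be between groups. The groups are independent, so McNemar would still be the wrong test.

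**What the scheduled data allow.** They allow a comparison of independent proportions, or of independent scores, at Visit 3 between alcohol and control.

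**The case against.** The strongest counter-argument is that the schedule, not the test, may be at fault. The visit lists are visibly incomplete. Table 1 has no questionnaire row although Visit 3 requires one. Table 1 also marks the sugar test and stool sampling at screening, where the visit text mentions only handing out the material. Those two home-collected items have both a screening and a Visit 3 mark, and the word *dependent* fits a baseline questionnaire that was meant but left out. This stands as a possibility. It does not remove the inconsistency, because no passage places a questionnaire before the drink, but the repair must leave room for it.

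It is also fair to say that the instrument is peripheral. Section 5 does not list it among the endpoints, the correlation list in Section 8.2.4 omits it, and Section 8.1 calls the trial a pilot. This stands in full and sets the grade.

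A later analysis plan might choose another test. That does not answer the point: the protocol does not leave the matter open, but names a test that its own schedule cannot feed.

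A reader might infer more than the documents support in three ways:

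- That McNemar could not be run at all. It could technically compare two binary items within the same Visit 3 form. The protocol describes no such comparison, and it would not address the effect of the drink.
- That the sponsor means to assume everyone was symptom-free beforehand and count any later symptom as change. No passage says so.
- That an independent-groups test would have good power at this size. The protocol gives no symptom rates, no item count and no split of the 30 controls, so it supports no power statement, and none is needed here.

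**Conclusion.** The rule is wrong as written, and the point is minor. Under the schedule as it stands, the questionnaire yields 0 before/after pairs and 0 between-group pairs among 46 subjects, so the planned McNemar comparison cannot be made.

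This rests on two readings: that the visit text is complete in giving the questionnaire once, and that the groups are unmatched, as nothing in the protocol suggests otherwise. If a baseline questionnaire was intended, the fault lies in the schedule. The two sections must be reconciled all the same, and McNemar would then describe change within a group but would not compare alcohol with control.

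A reader might take the mismatch as a threat to the trial's main result. It is not one: the primary endpoint is stool zonulin, and the questionnaire feeds no listed endpoint.

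**What to change.** Choose one of two repairs, according to what was intended.

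1. **Questionnaire given once, as scheduled.** In Section 8.2.4, replace McNemar with an independent-groups comparison of alcohol with control at Visit 3: Fisher's exact test for binary items and the rank-sum test for ordinal items or scores, each with the difference and its 95% CI. State in advance which control contrast is meant (one of the control drinks or all 30 controls together), since the protocol ranks none of them.
2. **Baseline questionnaire intended.** Add the same questionnaire before the drink to the visit text. Keep McNemar for within-group change in binary items only, and still add the between-group comparison from repair 1.

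In either case, add a questionnaire row to Table 1.

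The first repair costs one sentence in Section 8.2.4 and one table row, with no new data. The second also costs one extra form per subject and a line in the visit text, and is possible only for subjects who have not yet had the drink.

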## **5 Endpoints**

Primary endpoint

stool zonulin levels

Secondary endpoints

bacterial translocation

gut permeability

bacterial translocation

inflammation

innate immune function

gut microbiome

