#### Schedule of assessments

| Visit no.                                                                                                         | 1 (Screening)               | 2 | 3                  |
|-------------------------------------------------------------------------------------------------------------------|-----------------------------|---|--------------------|
| Timing                                                                                                     | 0-28 days prior to visit 1a |   | 24h after visit 1a |
| Inclusion / exclusion criteria                                                                                    | X                           |   |                    |
| Demographics/relevant medical history/current medical conditions                                                  | X                           | X | X                  |
| Physical examination                                                                                              | X                           | X |                    |
| Standard laboratory tests                                                                                         | X                           | X |                    |
| Lactulose/Mannitol/Sucrose Test                                                                                   | X                           |   | X                  |
| pregnancy test (in women of childbearing age)                                                                     | X                           | X |                    |
| Blood sampling for gut permeability, bacterial translocation, oxidative stress and innate immune function (50 ml) | X                           | X |                    |
| Stool sampling                                                                                                    | X                           |   | X                  |
| Dosage administration, adverse events, Concomitant medications/therapies                                          | Ongoing data capture        |   |                    |

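### The tests named for the hourly blood markers use only volunteers with all five Visit 2 values; a mixed model on all available samples would avoid that loss

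*Protocol*

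**What the plan says.** Protocol section 8.2.4 sends every continuous variable to one pair of tests: "Differences in continuous variables over time (all other variables) will be assessed by ANOVA or Friedman tests". Which of the two is used turns on how the data are distributed. The software is fixed in the same section: "Data will be analyzed with SPSS 21". The type of ANOVA is not named, but a comparison over time within volunteers implies the repeated-measures form. No sphericity correction is mentioned.

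The Visit 2 description in section 7 sets the sampling: "Blood sampling via a venous access line before alcohol consumption and every hour for 4 hours". That is one baseline and four hourly draws. The schedule of assessments also marks a research blood sample at screening, without saying whether it enters the time analysis.

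Section 8.1 gives the size: "we intend to perform a pilot study on 46 healthy volunteers (16 in the alcohol group, 30 in the control groups". Section 5 names the primary endpoint as "stool zonulin levels"; the schedule places stool sampling at screening and Visit 3 only.

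**The concern.** Both named tests work on complete blocks. If one of a volunteer's five samples is missing for a marker, that volunteer contributes nothing to the test for that marker, although four valid measurements exist. A lost draw, a haemolysed tube or a failed live-cell assay is enough.

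The alcohol group has only 16 people, and the pilot is meant to gauge the size of the effect on gut permeability and innate immune function. The schedule lists bacterial translocation and innate immune function among the purposes of the blood sample, and both are secondary endpoints. These are the results that would lose precision.

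There is a smaller second point. Uncorrected repeated-measures ANOVA assumes sphericity. Hourly series, in which neighbouring hours usually correlate more than distant ones, tend not to satisfy it.

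**Working it through.** **Inputs from the protocol.** Alcohol group 16; total 16 + 30 = 46, which agrees with section 8.1; draws 1 + 4 = 5; significance level 5%. The protocol gives no power calculation, so there is no planned power to reproduce.

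**Assumed inputs.** The missing rate per draw m, the effect profile and the within-person correlation are all assumptions. So is the premise that each marker is measured at all five draws, which the protocol does not state marker by marker.

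**Step 1: complete rows.** With independent loss, the share of volunteers with all five values is (1 − m)^5. Complete-case analysis uses 80 × (1 − m)^5 of the alcohol group's 16 × 5 = 80 values; an all-available analysis uses 80 × (1 − m).

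| m | (1 − m)^5 | Complete of 16 | Lost | Values used, complete-case | Values used, all available |
|---|---|---|---|---|---|
| 1% | 0.951 | 15.2 | 0.8 | 76.1 | 79.2 |
| 2% | 0.904 | 14.5 | 1.5 | 72.3 | 78.4 |
| 5% | 0.774 | 12.4 | 3.6 | 61.9 | 76.0 |
| 10% | 0.590 | 9.4 | 6.6 | 47.2 | 72.0 |

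**Step 2: power of the planned F test without missing data.** For n complete volunteers, five times and compound symmetry with correlation ρ, the noncentrality is λ = n × Σ(μ_t − μ̄)² / (1 − ρ), referred to F(4, 4(n − 1)).

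- Profile A: means 0, 0.35, 0.7, 0.7, 0.35 SD and ρ = 0.5. The sum of squares is 0.343, so λ = 16 × 0.343 / 0.5 = 10.98 and power is 72%. With 15 complete volunteers power is 69%, with 12 it is 57%, and with 9 it is 42%.
- Profile B: a 0.5 SD plateau from hour 1 and ρ = 0.6. The sum of squares is 0.20, so λ = 16 × 0.20 / 0.4 = 8.0 and power is 57%.

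**Step 3: complete-case against all-available data.** These are simulations with n = 16 and samples missing at random and independently. The planned F test on complete rows is compared with a volunteer-plus-hour linear model on all values, a stand-in for a mixed model.

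| m | Profile A: complete-case / all available | Profile B: complete-case / all available |
|---|---|---|
| 2% | 67% / 72% | 51% / 55% |
| 5% | 57% / 68% | 44% / 54% |
| 10% | 43% / 65% | 35% / 51% |

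The gap is 4–5 points at 2%, 10–11 at 5% and 16–22 at 10%. At 1%, losing about one volunteer (16 to 15 in step 2) costs about 3.5 points. In the Profile A setting, type I error stayed near 5% for both analyses (4.5% to 5.4%).

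**Step 4: sphericity.** Simulated under AR(1) correlation of 0.5 to 0.9, uncorrected repeated-measures ANOVA had a type I error of 6.2–8.7% at a nominal 5%. With the Greenhouse-Geisser correction it was 4.3–4.8%.

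**Step 5: which mixed model.** An unstructured 5 × 5 covariance has 15 parameters. With 16 complete volunteers its Wald F equals T²/4, distributed as (15/12) × F(4,12). Referred to the F(4,15) critical value of 3.06, the true error is P(F(4,12) > 3.06/1.25) = 10.3%. Across 46 volunteers in four drink groups the error degrees of freedom are 46 − 4 = 42, the factor is 42/39, and the error is about 6.6%. The covariance structure and the degrees of freedom therefore matter.

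**The case against.** The strongest objection is that the protocol only names a test family. It does not say that incomplete volunteers are excluded, and missing-data rules and sphericity details commonly sit in a statistical analysis plan, which is not at hand. A reader might infer that the protocol prescribes exclusion; it does not. What stands is narrower: complete-row use is how the named tests work, and a later plan could avoid the loss only by departing from them or adding imputation.

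Second, all Visit 2 draws come from one venous line in one supervised stay, so a low missing rate is plausible. Losses may also cluster. If a blockage is equally likely to begin at any of draws 2 to 5, it removes 2.5 samples on average. At a per-sample rate of 5% or 10%, the share of volunteers affected is then 5m/2.5 = 10% or 20%, leaving 14.4 or 12.8 complete volunteers rather than 12.4 or 9.4. This is a fair limit on the larger figures.

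Third, a reader might infer that the most affected drinkers miss draws, so that the analysis selects mild responders. Nothing in the protocol documents this, and the calculations used random loss, so they cannot show it. If loss depends on the unseen response, a mixed model is not protected either.

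Fourth, Greenhouse-Geisser alone answers the sphericity point, so sphericity is no reason to abandon ANOVA. Fifth, Friedman is the protocol's provision for non-normal data, and a linear mixed model does not replace it unless skewness is handled. Both points stand and are taken into the fix.

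**Conclusion.** The point holds as an improvement in method for the hourly secondary blood markers, not as a contradiction or a demonstrated error. The named tests waste valid measurements when any sample is missing, and the named software offers a procedure that keeps them.

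The size rests on an unstated missing rate. At 1–2% per draw the loss is small: about 1 to 1.5 of 16 volunteers and 3–5 power points per marker. At 5–10% with independent loss it is material: 3.6 to 6.6 volunteers and roughly 10–20 points. The power figures also depend on the assumed profiles and correlations.

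A reader might infer that the trial's main result is threatened. It is not: stool zonulin has two samples, and a volunteer missing one gives no within-person change under any method.

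**What to change.** In section 8.2.4, separate the hourly Visit 2 blood markers from the other continuous variables and specify for them:

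- a linear mixed model (SPSS MIXED, REML) with fixed effects of hour, drink group and their interaction, using all available samples;
- a parsimonious covariance such as AR(1) or heterogeneous AR(1), estimated across all 46 volunteers, not an unstructured matrix in the 16 alcohol volunteers;
- Satterthwaite degrees of freedom;
- log transformation of skewed markers, with Friedman kept as a sensitivity analysis where residuals remain clearly non-normal, noting that it still uses complete rows;
- the Greenhouse-Geisser correction wherever ANOVA over time is retained.

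The cost is protocol wording, a different procedure in the same software and slightly more analysis work. No new data are needed. The model is valid only if samples are missing at random, so the number of missing samples and the reasons should be reported for each hour and drink group.

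### For non-normal data the plan prescribes Friedman's test, but stool markers (including the primary endpoint) and the urine permeability test have only two time points, where Friedman is a sign test and loses power

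*Protocol*

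**What the plan says.** Section 8.2.4 has one rule for all continuous outcomes: changes over time are tested by "ANOVA or Friedman tests, depending on the distribution of the data". No other test of within-person change in a continuous variable is named. The same section adds "Bonferroni correction for multiple testing will be used", without saying over how many tests, and "All tests will be performed on a 5% significance level".

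Section 5 names the primary endpoint as "stool zonulin levels". In the schedule of assessments (section 7, Table 1), the row "Stool sampling" is marked at visits 1 and 3 only, and so is the lactulose/mannitol/sucrose test. The visit 3 text confirms one urine and one stool collection after the drink. Section 8.2.1 measures "DAO, Zonulin and Calprotectin in serum and stool samples". Of these two sample types only blood is taken repeatedly: under visit 2 it is drawn before the drink and hourly for four hours, which gives five values.

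Section 8.1 plans 16 people in the alcohol group and 30 across the control groups, 46 in all. It gives no effect size, standard deviation or power.

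**The concern.** Friedman's test is a sensible rank test for the five-point blood series. The same rule, though, covers the stool and urine markers, which have two values per person. There Friedman ranks each person's pair as 1 and 2 and nothing else, so a tenfold rise in zonulin counts the same as a trivial one.

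ELISA concentrations and urinary sugar recoveries may well be skewed. If stool zonulin fails the normality check, the rule as written leads to this test for the within-person change in the primary endpoint. With 16 exposed people, discarding the size of each change costs a good deal of power. It also fits poorly with the aim in section 8.1, which is to learn how large the effect is.

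**Working it through.** **Inputs.** From the protocol: n=16 in the alcohol group (8.1); two time points for stool and urine (Table 1, visit 3); 5% level (8.2.4). The protocol states no power to reproduce; the only sample-size arithmetic is 16 + 30 = 46. Effect sizes and distributions below are assumptions.

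**Step 1: what Friedman becomes.** With k=2, no ties, and S of n people increasing, the rank sums are n+S (after) and 2n−S (before). Then

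chi² = 12/(n·2·3) × [(n+S)² + (2n−S)²] − 9n = (2/n)(5n² − 2nS + 2S²) − 9n = (2S−n)²/n, on 1 df.

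This is the sign test without continuity correction.

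**Step 2: true size at n=16, two-sided 5%.**
- Chi-square p-value: S=12 gives (24−16)²/16 = 4.0, p=0.0455, so it rejects at 12:4. The exact probability of 12:4 or more extreme is 2(1+16+120+560+1820)/65,536 = 0.0768, so the size is 7.7%.
- Exact p-value: 12:4 fails (0.077), so 13:3 is needed: 2(1+16+120+560)/65,536 = 0.0213. The size is 2.1%.
- Exact signed-rank test: attained size 4.4%.

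**Step 3: does the 7.7% generalise?** Size of the chi-square version:

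| n | Nominal level | True size |
|---|---|---|
| 10 | 5% | 2.1% |
| 14 | 5% | 5.7% |
| 15 | 5% | 3.5% |
| 16 | 5% | 7.7% |
| 30 | 5% | 4.3% |
| 46 | 5% | 5.4% |
| 16 | 2.5% (Bonferroni, 2 tests) | 2.1% |
| 16 | 1.0% (Bonferroni, 5 tests) | 0.4% |

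With 3 or 4 tests at n=16 the size is 2.1% against nominal 1.67% or 1.25%. The direction of the error is not consistent.

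**Step 4: power at n=16, unadjusted 5%.** The effect is a shift in units of the SD of the within-person differences (log-scale differences for lognormal data). For the exact sign test at 0.8 SD, P(increase) = Φ(0.8) = 0.788, and the probability of 13 or more increases out of 16 is 0.551. Taking logs does not change the direction of a change, so this holds for lognormal data on either scale. The signed-rank figures and the heavy-tailed sign-test figures come from simulation with 100,000 replicates. The lognormal settings for the simulated figures combine a between-person log SD of 0.5 or 1.0 with an SD of log differences of 0.3 or 0.5.

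| Data | Shift (SD) | Exact Friedman/sign | Exact signed-rank |
|---|---|---|---|
| Lognormal, raw values | 0.5 | 22% | 36–40% |
| Lognormal, raw values | 0.75 | 49% | 67–73% |
| Lognormal, raw values | 0.8 | 55% | roughly 73–79% |
| Lognormal, raw values | 1.0 | 76% | 89–93% |
| Lognormal, logged values | 0.8 | 55% | 82% |
| Laplace differences | 0.8 | 75% | 87% |
| t(3) differences | 0.8 | 86% | 93% |

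The raw lognormal range at 0.8 SD varies with the spread assumed; the four settings above give 73–78%. A paired t-test on logged values has about 85% at 0.8 SD.

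**The case against.** **Friedman is used only when the data are not normal, so power for normal differences is the wrong illustration.** This stands. On the normal branch the plan uses ANOVA, which for two paired values is the paired t-test. For that reason the comparison above uses skewed and heavy-tailed data. The loss is modest for symmetric heavy tails (about 7–12 points at 0.8 SD) but remains clear for lognormal data.

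**A reader might infer that the plan's type I error is 7.7%, or that the test is anti-conservative in general.** The documents do not support this. The figure needs exactly 16 complete pairs, an unadjusted 5% level and the chi-square p-value. One missing stool sample turns 7.7% into 3.5%. A Bonferroni correction is planned but its number of tests is not given, and section 8.2.4 does not say whether p-values are asymptotic or exact.

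**A reader might also infer that Friedman is the settled primary test.** Section 8.2.4 names no test for the primary endpoint as such, and does not say whether changes over time are tested in the alcohol group alone or in all 46. The point is conditional: if stool zonulin is judged non-normal, the stated rule leads there.

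**This is a pilot, the exact sign test is valid, and the detail could sit in a SAP.** Validity is conceded, and the sign test does assume less than the signed-rank test. But the protocol has already named the test, so a SAP that followed it would inherit the weakness. With 16 people, the information lost matters even in a pilot.

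How the alcohol and control groups are compared is a separate question, which this point does not address.

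**Conclusion.** The point holds as a matter of efficiency for the two-time-point stool and urine markers, including the primary endpoint, whenever the non-normal branch is taken. That Friedman reduces to the sign test is exact algebra in the absence of ties. At n=16 and an unadjusted 5%, the exact version spends only 2.1 of the 5 percentage points. For lognormal data at an assumed 0.8 SD log-scale shift it gives up roughly 18 to 24 points of power against the signed-rank test on raw values (73–79% less 55%), and 27 points on logged values (82% less 55%).

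The power figures rest on assumed effects and distributions, because the protocol gives none; the size figures need only n, the level and no ties. The chi-square version's size is erratic, moving with n and with the Bonferroni level, and is not shown to be inflated overall. The plan should be changed here, but the exact form of the test it names is not invalid.

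**What to change.** In section 8.2.4, add a sentence to this effect: stool and urine markers measured at two time points are compared within person by the exact Wilcoxon signed-rank test when non-normal, preferably on log-transformed values, or by a paired t-test on the log scale where that is adequate; Friedman's test is kept for the five-point hourly blood series.

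This adds no visit, sample or participant. The signed-rank test brings an assumption the sign test does not need, that the differences are roughly symmetric; the log scale supports it for positive, right-skewed markers. Section 8.2.4 says "Data will be analyzed with SPSS 21", so the study team should confirm that its installation gives the exact p-value before the wording is fixed.
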